## **6.2 Regime allocation**

Women will be randomized in blocks of ten (each block with 1 SP group and 3 each of the other three groups). Random numbers between 1 and 800 will be generated by the computer (EPI INFO) programme and allocated to regimens until 80 numbers are in the SP+ placebo group and 240 each in the three other treatment groups. On consenting to participate, patients will be registered numerically in the enrolment log as they present. The registration number will determine the drug regimen.

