**PROPOSED STARTING DATE: Nov 2003 DURATION: 2 years**

**1) SUMMARY**

Pregnant women are vulnerable to malaria, with significant implications both for their health and for the pregnancy. Sulfadoxine-pyrimethamine (SP) is currently the first line drug for the treatment of malaria in pregnancy in Tanzania and surrounding countries, but resistance is emerging rapidly. Alternative drugs must be found, and new drugs and drug combinations are being recommended by many for deployment as first line treatment at the point that SP resistance forces a policy change. However, there are few data on the safety and efficacy of these combinations in pregnant women. This randomised trial aims to assess efficacy and safety, including birth outcome, in pregnant women with malaria in the second or third trimesters. A total of 900 pregnant women will be randomised either to standard treatment (SP) or to one of three potential drugs, or drug combinations recently recommended by a WHO expert panel. These will be SP-amodiaquine, chlorproguanil-dapsone (Lapdap), and amodiaquine-artesunate. Primary outcome will be treatment failure at day 28. Secondary outcomes will include maternal side effects, foetal viability and birth outcome.

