## **4.3 The trial**

1. This will be a randomized controlled trial with four arms;
2. The slide reader assessing the primary endpoint will be blind to treatment allocation, and analysis will be performed by intention-to-treat;
3. Direct Observed Therapy (DOT) of all doses of study regimens will be employed;
4. Drug doses packed in blister packs, labelled with the patient number will be used where possible.

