## 7 Sample size and duration of study.

**NOTE ADDED Oct 2004- the sample size calculation in italics is the original one. There is a revision following slow recruitment due to local control measures. This is in normal font and blue.**

*Sample size has been calculated based on treatment failure as defined in section 4.1. If the response of pregnant women to antimalarial treatment is similar to that of children in Muheza, the proportion of women with treatment failure by day 28 in the SP+Placebo group will be at least 45%, the parasitological clearance failure rate among sick children at the study site ([name] et al., 2001). A Cochrane data review of studies of amodiaquine in Africa showed a day 14 clearance failure rate on amodiaquine alone was 17% (Olliaro and Mussano, 2000) leading to a theoretical failure rate for SP+Amodiaquine of at least 8% ( $0.45 \times 0.17$ ) if there is no interaction between these drugs. In the Gambia, day 14 failure rate with SP+Artesunate was 1.6% (von Seidlein et al 2000). Assuming the 28-day failure rate of 4% with artesunate alone, the failure on amodiaquine+artesunate is estimated at at least 1% ( $0.17 \times 0.04$ ). In this study, it is assumed that the best treatment would achieve 5% failure rate. We will consider anything up to 10% failure rate to be equivalent for public health purposes.*

*Allowing for a 10% defaulter rate approximately 40 women per group would be sufficient to detect a five fold decrease in the risk of treatment failure in the three combination groups compared to the SP group. However this sample size is insufficient for comparing the risk of treatment failure between the different combinations. It is important to compare the efficacy of SP+ amodiaquine versus the combination including artesunate as the latter combination is likely to be more expensive and hence advantage over the former needs to be defined. Thus, in order to detect a 4 fold difference in treatment failure between SP+Amodiaquine and amodiaquine+artesunate group (eg 8% vs 2%) with 95% precision and 80% power, we will enrol 80 women in the SP+placebo group and 240 women in each of the other three groups.*

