*Based on the sample size of 80 women on SP alone and 240 in each of 3 combination regimens while allowing for 10% loss to follow up, a total of 900 women will be enrolled in the study. According to records at MCH for year 2000, a total of 6,880 pregnant women (approximately 20 per day) attended the antenatal clinic, of which an average of 6 per day had complaints. We assume that 3 of the sick 6 will have falciparum malaria and that 2 of them will consent to participate. Therefore, it will take 450 working days to enrol 900 women and the duration of the study is estimated to be 2 years.*

*The sample size should be adequate and sufficiently robust to detect common side effects in pregnancy. Rare side effects can only be detected in large Phase 4 and post-marketing surveillance studies. This study should provide information which can allow such studies to be undertaken.*

**Oct 2004.** Vigorous measures to protect pregnant women in the district from malaria on a general background of reduced transmission of malaria in this area have fortunately led to substantial reductions in the number attending the antenatal clinic with clinical malaria. The investigators reviewed the data from other sites, and it is clear there is still likely to be a critical shortage of data on antimalarials in pregnancy from Africa, so a trial even with an ability to detect this relatively large difference is likely to be of considerable utility to policymakers. A revised sample size has been calculated to detect a difference at day 28 from 1% (the best likely failure rate in any arm) and 15% (above which no drug could be deployed). This gives a sample size of 72 in each arm when  $\alpha$  was .05 and  $\beta$  0.8. This would be capable of detecting common, but not rare, adverse events. The trial will continue on this basis due to the public health importance of this question.

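### Section 6.2 still allocates 1:3:3:3, so the revised target of 72 women in each arm cannot be met for SP: stopping at the revised size would give SP 24 to 29

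*Protocol*

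**What the plan says.** Protocol section 4.3 fixes the design: "This will be a randomized controlled trial with four arms".

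Section 6.2 sets the allocation: "Women will be randomized in blocks of ten (each block with 1 SP group and 3 each of the other three groups". The numbered list runs to 800, "until 80 numbers are in the SP+ placebo group and 240 each in the three other treatment groups".

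These counts match the original calculation in section 7: "we will enrol 80 women in the SP+placebo group and 240 women in each of the other three groups". With an allowance for 10% loss, that calculation gives the 900 in the Summary: "A total of 900 pregnant women will be randomised either to standard treatment (SP".

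The October 2004 text in section 7 then resizes the trial, because of slow recruitment, to detect 1% against 15% failure at day 28: "This gives a sample size of 72 in each arm". It says that the trial proceeds on that footing. The accompanying note marks only the italic sample size calculation as the original. It does not mention section 6.2, and nothing elsewhere changes the ratio, the block or the list.

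Section 9 discontinues an arm when 50 women are enrolled in it, if 40% or more need escape medication. It expects about 45% on SP.

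**The concern.** The new size was put into section 7 but not into the section that assigns women to treatment. A per-arm figure that presumes equal arms now sits beside a rule that gives SP one woman in ten.

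SP is the standard-treatment arm. If the site follows section 6.2 and recruitment ends near the revised size, SP falls far short of the stated 72. The power attached to 72 then does not carry over to comparisons with SP. Arm sizes are settled by allocation, so an analysis plan cannot restore them afterwards.

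**Working it through.** **Inputs.** Section 7, October 2004: 1% v 15%, alpha 0.05, power 0.8 (printed as the value of beta), 72 in each arm. Section 6.2: blocks of ten at 1:3:3:3. Section 4.3: four arms. Original calculation in section 7: at least 45% failure on SP, and a five-fold decrease (45%/5 = 9%). Assumption: two-sided test, since sidedness is not stated.

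**1. Reproducing 72.** With p1 = 0.01, p2 = 0.15, mean 0.08, difference 0.14:

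n = [1.96·√(2·0.08·0.92) + 0.842·√(0.01·0.99 + 0.15·0.85)]² / 0.14² = 57.8

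Continuity correction: n' = (n/4)·[1 + √(1 + 4/(n·0.14))]² = (57.8/4)·[1 + √1.495]² = 71.3, rounded up to 72.

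The stated figure is reproduced with equal arms, a two-sided test and the correction. Without the correction it is 58; one-sided with the correction it is 59. Taking the printed value literally as beta (power 0.2) gives about 10, or 22 corrected. So 0.8 is the power and the label is a slip.

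**2. What 1:3:3:3 delivers.**
- Other arms at 72: SP = 72/3 = 24, total 24 + 3 × 72 = 240.
- Total 4 × 72 = 288: SP = 0.1 × 288 = 28.8, about 29; each other arm 0.3 × 288 = 86.4, about 86.
- SP at 72: total 72 × 10 = 720, with 216 in each other arm.

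**3. Power for SP against one alternative arm** (two-sided Fisher exact test at 0.05, full enumeration, SP the worse arm):

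| SP v other failure | 72 v 72 | 29 v 86 | 24 v 72 |
|---|---|---|---|
| 15% v 1% | 87% | 78% | 68% |
| 45% v 15% | 97% | 87% | 79.5% |
| 45% v 9% | >99% | 98% | 95% |

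The 72 v 72 entry exceeds 80% for 15% v 1% because the continuity-corrected formula is conservative here.

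**4. The section 9 threshold.** At one SP woman in ten, 50 on SP requires 50 × 10 = 500 women in total. That is well above 240 or 288, so the SP arm would not reach the point at which the rule acts.

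**The case against.** The unequal ratio was deliberate. The original calculation in section 7 says that about 40 women per group would be enough to show a five-fold drop from SP, and puts the larger numbers where the harder comparison lies, among the alternatives. SP failing at 15% is not the protocol's premise; 45% is, and there even 24 v 72 has about 80% power against 15% and 95% against 9%. This stands. A reader might infer that comparisons with SP are underpowered in general, and the protocol's own assumptions do not support that. The loss concerns the 1% v 15% contrast that the revision names.

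The 24 to 29 is also conditional. The protocol gives neither a revised total nor the number randomised by October 2004, and the 288 is inferred as 4 × 72. This stands too.

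Three further readings are tempting and should not be pressed:
- That section 6.2 describes two incompatible schemes, blocks and a free draw over 800 numbers. It reads naturally as one: 80 blocks of ten make exactly 800 numbers, 80 for SP and 240 for each other arm.
- That three totals are in force. The 800 and the 900 belong to a single superseded plan, before and after the allowance for loss. The conflict is between that plan and the revised one.
- That the misprinted beta undermines the 72. It does not, as step 1 shows.

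None of this reconciles the text. If 1:3:3:3 was kept on purpose, 72 in each arm is wrong. If 72 in each arm was meant, section 6.2 is wrong.

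**Conclusion.** The inconsistency is real and lies in current text, not in an amendment log. Under section 6.2 the SP arm would hold 24 women (others at 72) or about 29 (288 in total), which is 33 to 40% of the stated 72 (24/72, 29/72).

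For 15% on SP v 1%, power is 68% or 78%, short of the planned 80%. At 45% failure on SP the comparison stays adequately powered, at about 80 to 87% against 15% and about 95% or more against 9%. The practical harm is therefore a stated arm size and power that SP comparisons do not receive, plus a section 9 threshold that the SP arm would not reach. It is not the loss of any ability to detect a poor SP result.

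This rests on a two-sided test, recruitment ending near the revised size, and no unreported change of ratio.

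**What to change.** State one ratio and one total in sections 1, 6.2 and 7, by one of two routes.

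- **Keep 1:3:3:3.** Replace 72 in each arm with the true sizes. For example, 27 blocks of ten give 270 women: 27 on SP and 81 in each other arm, or about 24 and 73 after 10% loss (27 × 0.9 = 24.3; 81 × 0.9 = 72.9). Limit the 1% v 15% power statement to comparisons among the three alternative arms, and give SP comparisons their own figure: at 24 v 72, 68% for 15% v 1% and about 80% for 45% v 15%. The existing list can simply end after block 27. The cost is wording and a less favourable stated power for SP.
- **Equal allocation, if 72 on SP is intended.** Amend section 6.2 from a dated amendment, issue a new list, and stratify the analysis by allocation period. This costs more: an approved amendment, and the consent-form revision that the protocol's ethics section attaches to amendments. The final split cannot be computed until the number already randomised is known.

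Under either route, reconcile section 9 with the chosen SP arm size. As a minor edit, print power 0.8 (beta 0.2) in section 7.

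### A single published block of ten (1:3:3:3), with the log number fixing the regimen and no stated concealment step, leaves a modest but avoidable risk of selection bias at entry

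*Protocol*

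**What the plan says.** Protocol section 6.2 (Regime allocation) sets the block: "Women will be randomized in blocks of ten (each block with 1 SP group and 3 each of the other three groups". It then describes the list: "Random numbers between 1 and 800 will be generated by the computer (EPI INFO) programme", with numbers "allocated to regimens until 80 numbers are in the SP+ placebo group and 240 each in the three other treatment groups". On enrolment: "On consenting to participate, patients will be registered numerically in the enrolment log as they present". The link to treatment is direct: "The registration number will determine the drug regimen".

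Section 4.3 gives the only statement on blinding: "The slide reader assessing the primary endpoint will be blind to treatment allocation". It also says "Direct Observed Therapy (DOT) of all doses of study regimens will be employed" and "Drug doses packed in blister packs, labelled with the patient number will be used where possible". Section 6.3 has project nurses giving the drugs on one research ward.

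Section 6.1 lists SP as a single dose and the other three regimens over three days. SPAQ and AQAS each use two products. Sections 6.2 and 7 (Sample size) give the control arm a placebo, but section 6.1 lists none, and no double-dummy or matching of appearance is described.

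The October 2004 note in section 7 (Sample size) changes the target to 72 women in each arm. Section 6.2 keeps the 1:3:3:3 block and the totals of 80 and 240.

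**The concern.** Random allocation protects a comparison only if the person deciding whether and when to enter a woman cannot foresee her arm. Here the block length and make-up are printed, numbering is sequential, and nothing stated stands between the next number and its regimen. Taking consent before registration does not help if the next arm can be worked out before a woman is approached.

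There is room for judgement at entry. Under section 5, a study Medical Officer examines every referral from one clinic, and some criteria in sections 5.2 and 5.3 are matters of opinion, such as ability to attend follow-up or disease that would mask the response. There is also a possible motive, because section 7 (Sample size) expects at least 45% failure on SP.

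Baseline condition bears on the outcome. Women may enter with anaemia (section 5.2), and a fall in haemoglobin leading to rescue counts as failure (section 4.1). Neither a blinded slide reader nor analysis by intention to treat repairs selection that happens before registration.

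**Working it through.** **Inputs.** Block of ten, 1 SP and 3 each of SPAQ, Lapdap and AQAS; list 1-800; totals 80/240/240/240 (all section 6.2). Revised target 72 per arm (section 7, Sample size, October 2004). Assumptions: random order within each block, and an observer who knows the block rule and has seen earlier allocations.

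**1. The plan's own totals.** 800/10 = 80 blocks. 80 × (1, 3, 3, 3) = 80/240/240/240, which matches section 6.2 exactly.

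**2. Guessing the next arm.** The best guess is the arm with most slots left. Enumerating every possible block state gives the chance of a correct guess by position:

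| Position | 1 | 2 | 3 | 4 | 5 | 6 | 7 | 8 | 9 | 10 |
|---|---|---|---|---|---|---|---|---|---|---|
| Correct | 0.300 | 0.333 | 0.375 | 0.396 | 0.414 | 0.450 | 0.493 | 0.525 | 0.600 | 1.000 |

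The exact sum is 4.887 per block of ten, or 48.9%. Without tracking, the best guess is any one of the three new regimens: 3/10 = 30%.

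**3. Allocations fully determined.** All remaining slots must belong to one arm.
- Position 10: always, 1.
- Position 9: the last two slots are the same arm, 3 × C(3,2)/C(10,2) = 9/45 = 0.20.
- Position 8: the last three are the same arm, 3 × C(3,3)/C(10,3) = 3/120 = 0.025.

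The sum is 1.225 of 10, or 12.25%. Over 800 numbers that is 0.1225 × 800 = 98 women.

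**4. SP known to be used up.** The SP slot is equally likely to fall at any position, so it has been used before position k with probability (k−1)/10. The sum over k = 1 to 10 is 45/10 = 4.5 of 10 women, or 45%.

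**5. SP known or likely to be next.** This is what steering a woman away from SP would need.
- Certain: position 10 with SP unused, probability 1/10 per block, so 0.1/10 = 1% of women.
- At least 50%: add position 9 with SP unused (2/10), giving (0.1 + 0.2)/10 = 3%.
- At least one in three: add position 8 with SP unused (3/10), giving (0.1 + 0.2 + 0.3)/10 = 6%.

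**6. A longer fixed block.** The same enumeration for 20 (2:6:6:6) gives 44.3% correct guesses and 6.5% fully determined. Length alone helps only a little.

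**7. Ratio against the October 2004 target.** At 1:3:3:3, SP receives one woman in ten. Reaching 72 on SP needs 72/0.1 = 720 women. Enrolling 4 × 72 = 288 women gives 288 × 0.1 = 28.8, about 29, on SP.

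**The case against.** The strongest reply is that the headline figures do not measure the harm. Without tracking, predicting that the next woman will not get SP is already right 90% of the time, so knowing that SP is used up moves a recruiter only from at least 90% to 100%. Most of the gain from 30% to 48.9% lies in guessing among the three new regimens, where the expected failure rates are much closer (section 7, Sample size: at least 8% for SPAQ, at least 1% for AQAS). This stands, and it is why the SP-specific figures of 1% and 3% belong beside the others.

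The motive is also weaker than it looks. SP is national first-line treatment, and section 5.3 says women with mild disease excluded from the trial will generally receive it. Keeping a woman out may not spare her SP. The remaining route is to delay sicker women until the SP slot is used, which requires other eligible women to fill the places meanwhile. The October 2004 note reports substantially fewer cases. This too stands in large part.

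Four stronger readings are tempting but not supported:
- *That treatment is stated to be open.* The protocol never says so, and it names a placebo with SP. Visible allocation is a fair inference from section 6.1, not a stated fact.
- *That recruiters can read the next arm from numbered packs.* Appendix 2 keeps drugs locked and has the principal investigator issue them to a dispensing nurse. Nothing shows recruiters seeing unissued packs.
- *That section 6.2 contains two incompatible methods.* Step 1 shows that the totals are exactly what 80 blocks produce, so the 1-800 sentence may simply describe how the blocked list is made. It is unclear rather than contradictory.
- *That an unblocked list would lose the ratio if recruitment stopped early.* A random list keeps 1:3:3:3 in expectation. Only chance variation is added: at 288 women, about 29 on SP with a standard deviation of about 4.

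**Conclusion.** The point holds as a modest weakness in the method the protocol states, not as a gap in detail that an analysis plan would fill. A tracker would guess correctly 48.9% of the time against 30%, 12% of allocations would be determined, and SP would be known to be used up for 45% of women, but known to be next for only 1%.

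These figures assume that the block sentence governs the list and that staff can see earlier allocations. If the list is not blocked, the block figures fall away; the unconcealed link from number to regimen remains.

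A reader might infer that selection would favour the new drugs or undermine every comparison. The documents do not support that. Moving sicker women away from SP would flatter SP and understate the new regimens' advantage, and this mechanism hardly touches SPAQ against AQAS, the comparison that drove the sample size before October 2004. Nor is there evidence that steering happened; this is a risk.

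Separately, section 6.2 was not brought into line with 72 in each arm and needs rewriting on that ground alone.

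**What to change.** Rewrite section 6.2 for the remaining enrolment so that it states one method:
- permuted blocks of randomly varying size, in the allocation ratio of the revised design;
- block sizes kept out of the protocol text that recruiters see;
- the list held by existing personnel who do not recruit, away from the recruiting staff;
- the regimen revealed from sequentially numbered, sealed, opaque envelopes, opened only after eligibility and consent are logged.

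Replace the sentence that fills arms to 80 and 240 with the revised totals and a plain statement that the list is blocked. State also whether any placebo is used, so that the reader knows who can see the allocation.

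The cost is a new computer list and a set of envelopes. Balance between arms at any given moment will be slightly looser than with fixed blocks of ten.

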## **6.3 Clinical treatment and investigations.**

All women enrolled will be admitted to the research ward (to be built by the GMP) for the first three days for DOT and to monitor clinical response and adverse events. Drugs will be administered by nurses employed by the project. After each administration, the patient will be observed for 45-60 minutes to ascertain drug retention. The dose will be repeated if vomiting occurs within the observation period, and any further vomiting will cause withdrawal from the study and treatment with parenteral quinine. Patients will be treated for symptoms by standard treatment e.g. paracetamol for fever. Women will also continue to receive routine antenatal medicaments of iron supplements, folic acid, and Tetanus Toxoid (TT) given by the MCH. Drugs with an antimalarial activity will not be permitted; if these are essential, the subject will be withdrawn.

Vital signs (temperature, pulse) will be monitored eight hourly during the treatment period and once daily during the remaining period of hospitalisation. Blood pressure will be measured once daily during hospitalisation. Patients will be interviewed using a “clinical assessment form” check list which includes: weakness, chills/rigors, headache, myalgia, dizziness, abdominal pain, anorexia, nausea, vomiting, diarrhoea, palpitations, insomnia, pruritus, coughing, and tinnitus. Blood glucose will be measured on admission and regularly through treatment by glucose stix testing.

Foetal viability (presence of foetal heartbeat) will be monitored daily during admission using a Doppler machine, and at each follow-up visit.

